**Methods:**

The 13-armed randomized controlled trial aimed to assess the effectiveness of a mobile app-based self-guided psychological intervention delivered *via* a smartphone app (*Nałogometr*) in reducing craving and lapse risk in problematic alcohol or stimulants use. Participant recruitment and data collection will be performed from June 2022 to September 2022. The 4-week mobile intervention program will include short-term and long-term intervention modules based mainly on mindfulness and cognitive-behavioral therapy. Intervention effectiveness assessment will include Ecological Momentary Assessment. That is, we will collect longitudinal data on a set of characteristics of day-to-day functioning. The primary outcomes will include a self-reported number of lapses and addiction craving level. In contrast, the secondary outcomes will be the severity of problematic substance use, anxiety and depression scores, and life satisfaction scores.

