### 2.2 Participants

Recruitment takes place from June 2022 until September 2022 to ensure the targeted sample size is reached. Participants will be recruited *via* newsletters, advertisements, and social media. The study will be conducted using the proprietary mobile application *Nałogometr* to collect all relevant measurements. Inclusion criteria will include self-reported problematic alcohol or stimulant use, being 18 or over, speaking Polish fluently, using Android or iOS smartphones, and accepting informed consent. We recruit only people living in Poland.

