**FIGURE 1 F1:**
[figure not shown]
Participant flow chart.

The study will take place from June 2022 until September 2022, with ongoing participant recruitment. The study includes ecological momentary assessment (EMA), assessing several variables important linked to lapse risk. Participants will be asked three times daily to answer questions about their mood, psychological and physiological state, craving, and if lapses occur. EMA will be administered daily between 6 a.m. and 12 a.m (morning EMA) and between 4 p.m. and 10 p.m. (evening EMA). Participants can select a specific time for assessment delivery that best suits their schedule and needs. When prompted to complete the EMA, participants will have the time to complete it until the next scheduled. Assessments are designed to take less than 2 min to complete. In addition, participants will be able to initiate assessments themselves to not skip any measurements for the day.

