### 2.8 Measures

Sociodemographic data include gender, age, and place of residence. Substance use-related questions include frequency of use, lifetime use, treatment seeking, and abstinence period (see Supplementary Tables 1, 2). The study includes EMA (three times a day) assessing several variables: craving, lapses, mood, arousal, pressure, anxiety, procrastination, loneliness, tiredness, anger, hunger, and uncertainty (see Supplementary Table 3).

Moreover, the questionnaire assessment will occur three times during the study period (see Table 2).

**TABLE 2 T2:** Timeline of the questionnaire assessment.

Assessment instrument	Baseline (week 1)	Follow-up (week 5)	Follow-up (month 6)
Socio-demographic questions	*x*		
Substances use-related measures			
Psychological dependence (SDS)	*x*	*x*	*x*
Alcohol (AUDIT)	*x*	*x*	*x*
Stimulants (DUDIT)	*x*	*x*	*x*
Psychopathological symptoms measures			
Depression and anxiety (HADS)	*x*	*x*	*x*
Psychological functioning measures			
Sensation seeking (BSSS)	*x*	*x*	*x*
Emotion regulation (DERS)	*x*	*x*	*x*
Impulsivity (UPPS-P)	*x*	*x*	*x*
Coping with stress (Mini-COPE)	*x*	*x*	*x*
Life satisfaction (SWLS)	*x*	*x*	*x*

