### 2.9 Data analysis

We will use factorial design mixed-effects models to compare questionnaire battery scores between experimental groups and the control across measurements. In addition, we will perform an interrupted time series analysis to compare the longitudinal effects of the introduction of different types of interventions on longitudinal EMA outcomes.

We will include participants who complete at least 21 EMA assessments spread across the intervention testing period of 5 weeks. Furthermore, for the 6-month follow-up intervention effects retention analysis, we will include participants who complete at least three EMA assessments within the follow-up period. Moreover, in each intervention group, we will retain participants who log onto the app and use the long-term and short-term self-guided intervention modules at least four times and once, respectively, defined as minimal therapeutic exposure. Finally, for the secondary outcome analysis, we will include participants who complete the baseline and at least one follow-up assessment.

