### 2.10 Data management

As described above, all data will be collected continuously throughout the duration of the study *via* the *Nałogometr* mobile app, available on App Store and Google Play, and stored on a secured server. Key project personnel, i.e., Principal Investigators (PIs) and Co-Investigators (CIs) will be the data steward and will be responsible for documenting and managing the data during the collection, analysis, and publication phases. Additional project personnel, i.e., project coordinators, data analysts, and data scientists, will receive the data as per instructions from the PIs and CIs in an anonymized format. Following publication processes, the data will be archived and stored on a similarly secured server.

Data documentation will include codebooks that document the following: data collection protocols, methodology, and sample; description of specific data sources, e.g., types of measures that correspond to each raw data unit.

As per the needs of the particular project phase and according to current research questions, data will be queried and exported as ASCII files and made available to the additional project staff. Such datasets will include an individual (anonymized) participant identifier code, demographic information, relevant variable labels, and values. According to the current research questions, additional project staff will perform any data transformations necessary for the final and published analyses. Any publications that result from the data collected will be prepared only with the use of anonymized (de-identified) datasets and will pertain only to aggregate-level results. Due to the expected absence of (high) risks for participants of this study, establishing a data monitoring committee is not necessary.

It will be the responsibility of each additional staff member to produce documentation of what and how were the data used for the research task they were involved in. This will include documentation on the decisions related to any data transformations and coding performed (including variable lists and definitions of the raw data used and how the derived variables were produced), as well as the analytical methods and techniques performed for any particular research task.

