## 3 Discussion

This study protocol describes a randomized controlled trial designed to determine the effectiveness of self-guided psychological intervention modules delivered *via* a smartphone app (*Nałogometr*). We aim to examine whether and which interventions can effectively reduce craving and lapse risk in problematic alcohol or stimulant use. The embedded trial and analysis will evaluate the effectiveness of intervention modules for alcohol or/and stimulants use. In exploratory analyses, we investigate whether user engagement moderates or changes in psychological functioning measures (e.g., sensation seeking, impulsivity, stress coping, emotion regulation) mediate the effectiveness of the interventions. We hope to determine if these interventions delivered through mobile devices can be effective and contribute to future prevention or therapy addiction programs. The wide availability and accessibility of developed interventions are a substantial advantage. Mobile app interventions may reduce treatment barriers by staying anonymous and avoiding stigma and may be especially useful in places where professional help is unavailable (49–52). We plan a 6 months follow-up to conduct a longer-term evaluation and check the sustainability of the potential change in the user’s behavior–it is an essential factor for relapse prevention through the management of craving. Such a complex study of 13 conditions will allow us to understand better which long-term interventions are most effective. We include multiple intervention types to better assess their effectiveness across diverse individuals. One limitation of the present study could be that the participant dropout will be higher than expected based on previous research (53, 54). Due to the lack of personal contact with researchers and no additional incentives, e.g., prizes or monetary remuneration, the commitment to participate throughout the study may be lower, and motivation may decrease over time.

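### The stated June to September 2022 dates conflict with the month-6 follow-up, and the three-entry rule for the 6-month EMA retention analysis sets no timing near month 6

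*Protocol article*

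**What the plan says.** **Dates.** The abstract (Methods) states: "Participant recruitment and data collection will be performed from June 2022 to September 2022". Section 2.6, in the text after Figure 1, dates the whole study: "The study will take place from June 2022 until September 2022, with ongoing participant recruitment". Section 2.2 gives the same months for recruitment alone: "Recruitment takes place from June 2022 until September 2022 to ensure the targeted sample size is reached". Section 2.10 adds that "all data will be collected continuously throughout the duration of the study". No later collection period is dated anywhere in the article.

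**Follow-up.** Table 2 in section 2.8 schedules nine questionnaires at baseline, week 5 and month 6. The Discussion gives the purpose: "We plan a 6 months follow-up to conduct a longer-term evaluation and check the sustainability of the potential change in the user’s behavior".

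**Entry rules in section 2.9.** For the 5-week EMA analysis: "We will include participants who complete at least 21 EMA assessments spread across the intervention testing period of 5 weeks". For the 6-month retention analysis: "we will include participants who complete at least three EMA assessments within the follow-up period". The first rule asks for entries distributed over a named period. The second names a period that the article does not define, and it asks for no distribution within it.

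**The concern.** There are two separate problems.

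1. **Dates.** Enrolment and data collection cannot end in the same month if every participant is to be followed for 5 weeks and then to month 6. Taken literally, the dates yield no month-6 data and an incomplete 5-week period for late enrolees. The 5-week period carries the primary outcomes, lapses and craving.
2. **Entry rule.** The retention analysis is meant to show whether a change lasts to 6 months. Its entry rule asks how many EMA entries a participant made, not when. A participant could therefore be counted in a 6-month analysis without having been observed near month 6. The Discussion itself expects that commitment may be low and that motivation may fall over time, so early follow-up entries may be easier to obtain than late ones.

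**Working it through.** **Inputs.** Window of June to September 2022 (abstract; section 2.6), read as generously as possible as 1 June to 30 September. Enrolment over the same months (section 2.2). Assessments at week 5 and month 6 (Table 2). EMA three times daily, with self-initiated entries allowed (section 2.6). Entry thresholds of 21 and three EMA entries (section 2.9).

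**Step 1: month 6 against the window**

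| Enrolled | 5 weeks complete (+35 days) | Start of sixth month (+5 months) | Six months complete | Days from 30 Sept 2022 to six months |
|---|---|---|---|---|
| 1 June 2022 | 6 July 2022 | 1 Nov 2022 | 1 Dec 2022 | 62 |
| 30 Sept 2022 | 4 Nov 2022 | 28 Feb 2023 | 30 March 2023 | 181 |

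The longest follow-up that fits is 1 June to 30 September, 121 days, and 121 / 30.4375 = about 4.0 months. Even if month 6 means the start of the sixth month, the earliest possible date is 1 November 2022, 32 days after the window closes. On either reading no participant reaches month 6 within the stated dates.

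**Step 2: the 5-week period against the window**

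- Last enrolment date that allows 35 days by 30 September: 30 September − 35 days = 26 August 2022.
- Enrolment days after that date, 27 August to 30 September: 5 + 30 = 35.
- All enrolment days: 30 + 31 + 31 + 30 = 122.
- Share: 35 / 122 = 28.7%, or about 29% of participants if accrual is uniform. Uniform accrual is an assumption; the article gives no accrual pattern.

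**Step 3: what three entries can represent**

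This step assumes that the follow-up period runs from week 5 to month 6 with EMA continuing. The article does not say so.

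- Length, for a participant enrolled on 1 June: 6 July to 1 December = 148 days.
- Prompts at three a day: 148 × 3 = 444, and 3 / 444 = 0.7%.
- Prompts at two a day (section 2.6 describes only a morning and an evening window): 148 × 2 = 296, and 3 / 296 = 1.0%.
- At three a day, one day of entries is enough. With only two scheduled windows, one day is still enough if a self-initiated entry is added; otherwise two days are.
- For comparison, the 5-week rule asks for 21 of 35 × 3 = 105 prompts (20%), or 21 of 35 × 2 = 70 (30%).

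If the follow-up period is instead a short EMA block at month 6, step 3 falls away and three entries is only a minimum-data rule. Steps 1 and 2 do not depend on this assumption.

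**The case against.** **The dates are loosely worded, and collection was never meant to stop.** Section 2.2 gives the same months for recruitment only, and Table 2, section 2.9 and the Discussion all state the 6-month follow-up plainly. This is the likelier reading. A reader might infer from the dates that the sponsor plans to collect no month-6 data, or that 29% of participants will in fact be truncated. The document does not support that, because its own schedule says otherwise. The contradiction still stands: the abstract names data collection expressly and section 2.6 dates the study itself. An analysis plan that is not shown cannot remove a conflict printed here.

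**The follow-up period may be a block at month 6.** The article does not define it, and Table 2 uses month 6 as a time point. If a block was meant, the entry rule is sound. This makes the second problem conditional. It does not dispose of it, because Table 2 places questionnaires and not EMA at month 6, and so supplies no EMA window.

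**An entry threshold is not an estimator.** A reader might infer that durability will be overstated. That would need early entries to be pooled and reported as 6-month data, and the article describes no such step. Its EMA method is an interrupted time series analysis, which models time. This objection is right, and no direction of bias is claimed.

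**The whole 6-month evaluation is not at risk from the entry rule.** A reader might take the two problems together to defeat it. The three-entry rule is stated only for the EMA retention analysis. The month-6 questionnaires come under a different rule in section 2.9 (baseline plus at least one follow-up assessment) and are touched only by the dates.

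**Conclusion.** The point holds in two parts of different strength.

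- **Dates: firm.** The stated end of collection and of the study comes before month 6 for every possible enrolee, by 62 to 181 days (32 to 151 if month 6 means the start of the sixth month). It also comes before the end of the 5-week period for enrolments on the last 35 of 122 days. Only the conversion of those days to 29% of participants needs uniform accrual. It is most likely a drafting error, but the passages must be reconciled.
- **Entry rule: conditional.** The rule for the 6-month EMA retention analysis contains no timing requirement, although the rule beside it does. If the follow-up period runs from week 5 to month 6, a participant can qualify on one day's entries soon after week 5. Neither the size nor the direction of any effect on the retention result can be derived from the article.

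Correcting both would not give an untreated randomised comparison at month 6, because section 2.6 gives the waitlist group all intervention materials 5 weeks after enrolment.

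**What to change.** 1. **Reconcile the abstract and section 2.6 with Table 2, section 2.9 and the Discussion.** State three end dates. If enrolment closes on 30 September 2022, 5-week collection runs to 4 November 2022 and six months are complete for the last enrolee on about 30 March 2023.
2. **Define the follow-up period in section 2.9.** Require the EMA entries that qualify a participant for the 6-month estimate to fall in a prespecified window around month 6. Two weeks either side is one example; it would extend EMA collection for the last enrolee to about 13 April 2023 (30 March + 14 days).
3. **Model any earlier follow-up EMA by time since enrolment**, so that it informs the course over time without being read as 6-month data.

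The cost is a few lines of text and EMA prompts kept open until the last window closes. The drawback is that fewer participants will contribute to the 6-month EMA estimate. The month-6 questionnaire analysis needs only the corrected dates.

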##### 2.7.1.3 Self-guided psychological intervention modules

Two main self-guided intervention modules were created for a mobile app: (1) short-term self-guided intervention module and (2) long-term self-guided intervention module (Table 1 and Figure 2). The delivery of these interventions will be initiated 5 days following study enrollment.

**TABLE 1 T1:** Intervention modules in the mobile app.

Intervention modules	Description
Short-term interventions	This module consists of audio-guided sessions on gratitude, auto-empathy, thoughts management, and relaxation. Moreover, they are based on breath relaxation exercises, craving management, and motivation to change.

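### Section 2.9 filters the intervention arms, but not the waitlist arm, on module use after randomisation, so the comparison with control can show a difference when there is no treatment effect

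*Protocol article*

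**What the plan says.** All the inclusion rules stand in section 2.9 of the protocol article.

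- **Intervention arms only:** "in each intervention group, we will retain participants who log onto the app and use the long-term and short-term self-guided intervention modules". The thresholds are four uses for the long-term modules and one use for the short-term module, and the section presents them as the smallest exposure that counts.
- **All arms, 5-week period:** "We will include participants who complete at least 21 EMA assessments spread across the intervention testing period of 5 weeks".
- **All arms, 6-month EMA analysis:** "we will include participants who complete at least three EMA assessments within the follow-up period".
- **All arms, questionnaires:** "for the secondary outcome analysis, we will include participants who complete the baseline and at least one follow-up assessment".

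None of these is called per-protocol, supportive or sensitivity. The same section plans mixed models that compare the experimental groups with the control on the questionnaires, and an interrupted time series for the EMA outcomes.

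Section 2.6 says who can use what. Conditions 1 to 10 have the short-term module and one long-term module, condition 11 has the short-term module and all long-term modules, and condition 12 has the short-term module alone. Access in these twelve groups opens after 5 days. The waitlist group receives the materials 5 weeks after enrolment. The same section balances the arms on six baseline characteristics, among them addiction severity, abstinence duration and participation in therapy.

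**The concern.** How often a participant opens a module is behaviour after randomisation, and it probably depends on motivation, severity and how recovery is going. Twelve of the thirteen arms are cut down to those who reached a use threshold. The thirteenth cannot be cut in that way during the test period, because it has nothing to use. The balance that the allocation algorithm builds is then lost on exactly the characteristics likely to predict lapse and craving, and an inert module could appear to help or to harm.

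The Discussion also sets out to learn which modules work best. Four long-term uses is a different hurdle when one module is on offer (conditions 1 to 10), when all ten are (condition 11) and when none is (condition 12). The Discussion itself expects that commitment may be low, with no personal contact and no incentives, so the share removed may not be small. It also plans to explore engagement as a moderator, which concedes that engagement may be related to outcome.

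**Working it through.** **1. The plan's own figure.** Section 2.3 gives a minimum of 650 participants for 80% power, from a simulated random-intercept model with 21 entries each and a small effect. The article does not state alpha, the numerical effect, the intraclass correlation (ICC) or the contrast, so 650 can be neither confirmed nor refuted. Assume two-sided alpha 0.05 and SD of a person's mean = sqrt(ICC + (1 - ICC)/21). Totals then run from 118 (two equal groups, d = 0.3, ICC 0.3) to 14,586 (13 equal arms compared pairwise, d = 0.1, ICC 0.7). One assumed cell (twelve arms pooled against control, d = 0.3, ICC 0.5) gives 50 per arm and 13 x 50 = 650, but the article does not state those inputs. The point here does not depend on this figure.

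**2. Who is filtered on what, weeks 1 to 5.**

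| Arm | 21 EMA entries | 4 long-term uses | 1 short-term use |
|---|---|---|---|
| Conditions 1 to 10 | yes | yes, one module available | yes |
| Condition 11 | yes | yes, all modules available | yes |
| Condition 12 | yes | required, but no module available | yes |
| Waitlist | yes | cannot apply | cannot apply |

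**3. Bias with no treatment effect.** Let module use have correlation r with a favourable outcome, and keep the most engaged share p of an intervention arm. With c = z(1 - p) and a standard normal density, the retained participants differ from an unfiltered arm by

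bias = r x density(c) / p, in SD units.

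The multiplier density(c)/p is 0.350 at p = 0.8, 0.798 at p = 0.5 and 1.159 at p = 0.3. For example, r = 0.2 and p = 0.5 gives 0.2 x 0.798 = 0.16 SD.

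**4. With the EMA rule in both arms.** The same model was simulated (one million participants per cell) with a completeness filter applied first to everyone. Completeness was assumed to correlate 0.6 with module use, and 60% to pass.

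**5. Type I error.** With equal allocation (assumed) there are 650/13 = 50 controls and 600 in the pooled intervention arms, cut to 600p. The standard error is sqrt(1/(600p) + 1/50) at unit SD. For p = 0.5 it is sqrt(1/300 + 1/50) = 0.153. A bias of 0.16 is then 1.04 standard errors, and the nominal 5% two-sided test rejects about 18% of the time.

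| r | p | Raw bias (SD) | Bias after common EMA filter (SD) | Type I error, raw bias | Type I error, EMA-filtered bias |
|---|---|---|---|---|---|
| 0.1 | 0.8 | 0.035 | 0.014 | 0.056 | 0.051 |
| 0.1 | 0.5 | 0.080 | 0.049 | 0.082 | 0.062 |
| 0.1 | 0.3 | 0.116 | 0.083 | 0.112 | 0.082 |
| 0.2 | 0.8 | 0.070 | 0.029 | 0.076 | 0.054 |
| 0.2 | 0.5 | 0.160 | 0.096 | 0.181 | 0.096 |
| 0.2 | 0.3 | 0.232 | 0.163 | 0.305 | 0.175 |
| 0.3 | 0.8 | 0.105 | 0.043 | 0.109 | 0.060 |
| 0.3 | 0.5 | 0.239 | 0.145 | 0.347 | 0.158 |
| 0.3 | 0.3 | 0.348 | 0.244 | 0.585 | 0.332 |

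The last column does not reduce the sample sizes for the EMA filter. Smaller groups would lower it somewhat. With everyone kept, or with the same filter in both arms, the bias in this model is 0 and the type I error is 0.05.

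**The case against.** **Controls are filtered too.** This is correct. A reader might infer a contrast of engaged users with all controls, but controls must also reach 21 EMA entries and, for questionnaires, complete a baseline and one follow-up. These rules narrow the gap, as the fourth column of the table shows. They do not close it, because they select on logging and not on module use. At three prompts a day for 35 days, 21 entries is 21/105 = 20% of prompts, so the rule need not be a strict one.

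**The analyses use each person's earlier data.** Modules open after 5 days, so the interrupted time series has a pre-intervention segment, and the questionnaires have a baseline. Stable differences in level can therefore be removed, and the raw contrast above overstates the problem where that works. What remains is a difference in trend: motivated users may improve faster than unselected controls without any module effect. The same formula then applies with r as the correlation of engagement with change, a value that the documents do not give.

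**The rule may not reach the questionnaires.** Section 2.9 gives the secondary outcomes their own inclusion sentence and does not say whether the module-use rule also applies. On the narrower reading, the rule still governs both primary outcomes.

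**The article is condensed.** Section 2.4 refers to a pre-registration that is not shown. A reader might infer that no all-randomised analysis exists anywhere, and the article cannot support that. The point rests on the rule that it does state.

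**The direction is open.** A reader might infer that the long-term threshold selects the motivated while the short-term one selects people with craving, or that people who stop logging are those who lapsed. The document supports neither. Table 1 says of the short-term sessions that "they are based on breath relaxation exercises, craving management, and motivation to change", and it also lists gratitude, auto-empathy, thought management and relaxation, so use is not a marker of craving. If the selections oppose each other, the net bias may be small or reversed.

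**Conclusion.** The concern stands for the one-sided use filter. Followed as written, section 2.9 compares participants selected on engagement with controls who are not, and this can produce a difference without a treatment effect.

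The size is illustrative only: 0.035 to 0.35 SD for a raw level contrast and 0.014 to 0.24 SD after the assumed common EMA filter. The correlation, the share retained, the EMA filter's parameters and the single sign of the selection are all assumptions.

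A reader might conclude that the bias equals or exceeds the effect that the trial is designed to find. That is not shown. The article calls the effect small without a number. If 0.2 SD is assumed, three of the nine raw cells exceed it (all with r of at least 0.2 and at most half retained), and one of the nine does after the EMA filter.

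It would also go too far to say that the ranking of modules is biased. Conditions 1 to 10 face the same rule, so bias among them requires that uptake or selection differs between modules, which is possible but unknown. Condition 12 is different: read literally, no participant there can satisfy the long-term requirement. Sections 2.6 and 2.9 must be reconciled on this.

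**What to change.** In section 2.9, define the primary analysis as all randomised participants in the arm assigned, using every available EMA entry in the mixed model, with no module-use filter and no minimum number of entries. Keep the 21-entry set and the minimal-exposure set as labelled supportive analyses, and say how the exposure rule treats condition 12.

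An estimate of the effect among users, with assigned arm as the instrument, can be optional. It needs its exclusion assumption stated: that use below the threshold has no effect on outcome. With a cut at four uses that is doubtful, because one to three uses may do something.

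The change is to wording and needs no new data collection. It has two costs. The estimate becomes the effect of offering a module and is diluted by non-users. For instance, if half reach the threshold and lesser use does nothing, the effect of offering is 0.5 times the effect in users, and the same power needs 1/0.5² = 4 times the sample that would suffice if everyone used the module. The power basis in section 2.3, which assumes 21 entries per participant, should therefore be rechecked and restated for the all-randomised set.

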## 2 Methods

### 2.1 Aim

The study aimed to evaluate the effectiveness of long-term and short-term intervention modules in reducing craving and lapse levels in alcohol and stimulant problematic use.

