### 2.6 Randomization

Randomization will be applied using an automated balancing algorithm. The algorithm will aim to partition participants into groups based on the initial onboarding assessment to make the resulting groups as balanced as possible concerning the characteristics outlined in the study design section, i.e., (1) primary addiction type; (2) participation in addiction-related therapy; (3) gender; (4) age; (5) addiction severity; (6) abstinence duration. Following randomization, participants in groups 1–12 will receive access to the intervention modules following a 5-day delay. In conditions 1:10, participants get access to the short-term intervention module and one type of long-term intervention. In condition 11, participants get access to the short-term intervention module and all long-term interventions. In condition 12, participants get access only to the short-term intervention module.

Participants in the waitlist control group will be able to access all intervention materials 5 weeks following study enrollment (see Figure 1).

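### The minimal-exposure rule in section 2.9 requires long-term module use in every intervention group, so as written it can retain no one from arm 12, which has only the short-term module

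*Protocol article*

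**What the plan says.** Section 2.9 (Data analysis) sets inclusion rules in sequence: a minimum of 21 EMA assessments over the 5-week testing period, a minimum of three in the 6-month follow-up, and then an exposure rule. The scope of the exposure rule is "in each intervention group, we will retain participants who log onto the app", and its content is that they must also "use the long-term and short-term self-guided intervention modules at least four times and once, respectively, defined as minimal therapeutic exposure". A separate last sentence sets inclusion for the secondary outcomes by questionnaire completion.

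Section 2.6 (Randomization) defines access by arm:

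- All active arms: "participants in groups 1–12 will receive access to the intervention modules following a 5-day delay".
- Arms 1–10: "In conditions 1:10, participants get access to the short-term intervention module and one type of long-term intervention".
- Arm 11: "In condition 11, participants get access to the short-term intervention module and all long-term interventions".
- Arm 12: "In condition 12, participants get access only to the short-term intervention module".
- Control: "Participants in the waitlist control group will be able to access all intervention materials 5 weeks following study enrollment".

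Section 2.1 gives the aim as to "evaluate the effectiveness of long-term and short-term intervention modules in reducing craving and lapse levels". Nothing in the article exempts arm 12 from the exposure rule or limits the long-term threshold to arms that have a long-term module.

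**The concern.** The rule has two conditions, both required, and one of them cannot be met in a randomised arm. That arm has a particular job. Every other active arm offers the short-term module together with one or all long-term types, so a comparison of any of them with the waitlist estimates a combined effect. Only arm 12 shows what the short-term module does alone, and only a comparison with arm 12 shows what a long-term module adds to it.

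An analyst who meets an empty arm will probably relax the rule. That would be an unplanned choice of analysis population, possibly made after the data have been seen. Relaxing the rule for arm 12 only also creates a second problem: arms would be selected on different amounts of post-randomisation use.

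**Working it through.** The check is mainly logical. The one related figure in the plan is the minimum sample of 650 in section 2.3. It cannot be reproduced from the article, which gives the effect size only as small and states no intraclass correlation, significance level or tested contrast. Nothing below depends on reproducing it; 650 is used only as a head count.

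**Step 1. Apply the rule to each arm.** Retained if long-term uses ≥ 4 and short-term uses ≥ 1 (section 2.9), given access in section 2.6.

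| Arm | Long-term access | Short-term access | Can the rule be met? |
|---|---|---|---|
| 1–10 | one type | yes | yes |
| 11 | all types | yes | yes |
| 12 | none | yes | no: maximum 0, required 4 |

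So 11 of 12 intervention arms can contribute, and retention in arm 12 is 0% whatever its participants do. This takes section 2.6 at its word that arm 12 gets no long-term access.

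**Step 2. Head count.** The allocation ratio is not stated. With equal allocation, 650 / 13 = 50 per arm. Arm 12 is then 50 / 650 = 7.7% of those randomised, and the pool falls to at most 650 − 50 = 600. This is before the 21-assessment filter, so it counts randomised participants affected, not analysable participants lost.

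**Step 3. What is lost and what remains.** Counting all possible pairs of arms, which the article does not list as planned contrasts:

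- All pairs: 13 × 12 / 2 = 78.
- Pairs involving arm 12: 1 with the waitlist + 10 with arms 1–10 + 1 with arm 11 = 12, all lost.
- Pairs remaining: 78 − 12 = 66, made up of 11 × 10 / 2 = 55 among arms 1–11 and 11 with the waitlist.

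**Step 4. The lenient reading.** Suppose each threshold applies only where its module is offered. The minimum use needed to stay in the analysis is then:

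- arms 1–11: 4 + 1 = 5 uses;
- arm 12: 1 use;
- waitlist: none, since the rule covers intervention groups only.

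Arm 12 survives, but the groups are selected on different engagement criteria. The article gives no usage data, so neither the difference in retention nor the resulting bias can be sized.

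**The case against.** The best defence is that nobody would apply the rule literally. The word *respectively* ties each threshold to its own module, and the natural intention is that a threshold applies where the module is offered. Section 2.6 creates a short-term-only arm on purpose, and the Discussion relies on all 13 conditions. The article also cites a pre-registration that is not shown, which may define exposure by arm. It is fair to conclude that the authors probably do not intend to empty arm 12. But the text joins the two conditions and applies them to each intervention group without exception, and the lenient reading leaves the unequal filters of Step 4.

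Three stronger readings are tempting and are not supported:

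- *That losing arm 12 defeats half of the stated aim.* The Discussion stresses finding which long-term interventions work best. Arms 1–10 share the short-term module and can be ranked against each other, and compared with the waitlist, without arm 12. What goes is the short-term effect alone and the increment over it.
- *That planned contrasts with arm 12 are removed.* The article never names arm 12 as a reference. Section 2.9 speaks of experimental groups against control and of different intervention types. The use of arm 12 as a reference is inferred from the design.
- *That arm 12 disappears from every analysis.* The secondary outcomes have their own inclusion sentence, and whether the exposure rule applies on top of it is not clear.

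**Conclusion.** The point stands as a direct conflict between sections 2.6 and 2.9. Applied as written, the exposure rule retains no arm 12 participant, at least in the EMA analyses, which carry both primary outcomes. The 0% follows from the text alone; the figure of about 50 of 650 rests on assumed equal allocation. This is not detail left to a fuller document: the article states numerical thresholds and a scope that do not fit its own arms. The unequal selection under the lenient reading is real in direction of concern but unquantified. It should be corrected before any analysis, because the remedy is cheap and a later one would be made with the data in view.

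**What to change.** 1. Reconcile sections 2.6 and 2.9: define minimal exposure by the modules each arm can access, so that arm 12 is judged on the short-term element only. State whether the rule also applies to the secondary outcomes.
2. Run the main between-arm comparisons without the exposure filter and keep the exposure-defined set as a supportive analysis. Step 1 alone would leave different post-randomisation filters across arms.
3. If a supportive comparison of arms 1–11 with arm 12 is wanted in exposed participants, apply the short-term criterion to both sides. This equalises the criterion but does not guarantee equal selection: people who also have a long-term module may differ in whether they turn to the short-term one.

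The cost is a short edit to section 2.9 and a small change of analysis population. Including people who used little of the app may dilute the estimated effect. No new data and no change to the arms are needed.
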